## **PROJECT DESIGN**

Because the evolution of the COVID-19 pandemic is unpredictable we will utilise a simulated environment to establishing our core hypothesis about the effectiveness of MR telemedicine.

This is a prospective observational simulated trial designed to evaluate the impact of MR telemedicine technology (HL2) on care delivered during a simulated adult resuscitation.

**Recruitment:** Study participants will be recruited from a convenience sample of clinical staff who provide care to COVID-19 patients at Imperial College Healthcare NHS Trust and Imperial College London. This will include doctors in training and equivalent non-training medical staff, in addition to independent specialist nurse practitioners. All participants will have prior experience/qualifications in advanced life support skills and resuscitation. Informed consent will be obtained prior to commencing the study.

**Quality assurance and standardisation:** All team members will receive standardised training in two components of practice prior to entry into the study in order to familiarise themselves with the HL2 device and ensure basic technical competency:

1. HL2 operation: All participants will receive a standardised tutorial on how to operate the HL2 headset. This 15-minute practical induction will provide them fundamentals of use, namely a) how to wear PPE with the device b) how to turn on the device, access software and interact with the device c) how to make and receive calls and use clinical data. The training will be run as a hands-on demonstration/run-through clinical scenario provided by the study team in which participants will be able to familiarise themselves with the HL2 device and its use. All participants will be expected to perform a simple competency test before being allowed to proceed to the trial phase to ensure standardised basic technical competency and mitigate device related 'first-use' learning effects.
2. Advanced Life Support: All participants will be provided with a refresher instruction on core aspects of advanced life support according Resuscitation Council UK guidelines. Instruction provided will cover all knowledge and practical skills required to successfully complete each of the simulated clinical scenarios, including advanced airway skills. Clinical scenario protocols will be written by experienced simulation practitioners and based upon the guidelines for the management of in-hospital assessment and resuscitation of the critically unwell patient.

**Simulation study method:** The study will be conducted according to a randomised cross-over design. Participants will complete two simulated clinical resuscitation scenarios as part of a single half-day study session that will also include their standardised training. There will

be a wash-out period of at least 1 hour between each scenario. This is a deliberately pragmatic methodological approach that has been chosen to ensure sufficient participant recruitment and study completion given time demands on participants if the study were to be split across multiple sessions. Prior to commencing the first simulated scenario participants will be randomly assigned to one of two groups - standard care, or HL2 supported care - and will cross-over into the alternate group for the second scenario. The order of the test scenarios will be counterbalanced to mitigate any learning effects. The order of HL2/standard care will be determined by using sealed envelopes prior to starting the simulation. Participants will be required to undertake advanced airway skills in order to test the impact of HL2 on remotely supporting the delivery of vital clinical skills in high stress situations. The clinical scenarios will not be identical but will be based upon standardised clinical moulages undertaken for basic and advanced life support qualifications, and those undertaken by doctors in training as part of their core curriculum to ensure consistency, reliability and control for learning effects.

*Group 1 (Standard care)* - the participant will act as a first responder to a critically unwell patient with suspected COVID-19. They will be required to make an initial assessment, perform advanced life support and handover the patient to a senior clinician played by a member of the study team for successful completion of the scenario. The same study team member will act as the senior clinician for both study scenarios to reduce variability. A nurse, played by a member of the study team, will be provided to assist at the bedside, and senior clinical support will be available by telephone if required. This senior clinical support will again be standardised across all scenarios and provided by a member of the study team. Relevant clinical data and patient information will be available via a standard desktop electronic healthcare record system. Resuscitation algorithms and standard operating procedures will be provided on the desktop computer.

*Group 2 (HL2 supported care)* - in addition to standard care participants will complete the scenario whilst wearing an HL2 headset. A senior clinician, standardised across scenarios and played by a member of the study team to ensure consistency, will be available to talk and interact directly with the participant using voice and mixed reality prompts via the HL2 throughout the simulated scenario. The participant will be able to request 'heads-up' views of patient information and clinical data, in addition to resuscitation algorithms and standard operating procedures via the HL2 headset. All other standard material and equipment as per Group 1 will also be provided.

The simulation will be undertaken in a specialist simulation lab at Imperial College London facilitated and led by experienced simulation practitioners. The research team will be solely responsible for capturing observational data. A high-fidelity adult patient simulator (Laerdal) will be used to simulate an unwell adult with COVID-19. Vital signs will be standardized and pre-programmed with an adjustable override feature controlled by the study investigators. Before the start of each simulation session, study investigators will provide information to the participants on the patient using a standardised clinical moulage, with instructions to follow during the case, and the roles of study participants defined prior to the start of the simulation. Simulated medications, fluids, and equipment will all be available. Full PPE will also be available to all participants in the scenario. All scenarios will be video recorded, and these will subsequently be assessed by two independent researchers.

We aim to enrol 30 individual participants into the study who will undertake a total of 60 clinical scenarios (30 as standard care, 30 as HL2 supported care). The study will take place in a single setting - the study team anticipate this will last a maximum of 2hrs to allow for consent, initial technical training and the completion of 2x clinical scenarios.

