### 13. Participants

**13a. Number of Participants:** 30

**13b. Lower Age Limit:** 18

**13c. Upper Age Limit:** No restrictions

**13d. Birth Sex (male/female):** No restrictions.

**13e. Please provide justification for the sample size, and age/sex restrictions:** It is not possible to perform a power calculation for this work, as there are currently no data available on HL2 interventions upon which a standard deviation of the primary outcome measure can be calculated. The objective of this pilot study is therefore to determine a power calculation for a formal randomised control trial in patients.

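### The protocol counterbalances scenario order and randomises HL2/standard order but does not say the two are balanced or crossed, which risks chance imbalance and lost precision with 30 participants

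*Protocol*

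**What the plan says.** Protocol section 10, under the simulation study method, sets out the design: "The study will be conducted according to a randomised cross-over design". Condition order is random: "Prior to commencing the first simulated scenario participants will be randomly assigned to one of two groups", after which participants switch to the other condition. The means is given as "The order of HL2/standard care will be determined by using sealed envelopes prior to starting the simulation".

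Scenario order is handled in a separate sentence: "The order of the test scenarios will be counterbalanced to mitigate any learning effects". The two scenarios differ: "The clinical scenarios will not be identical but will be based upon standardised clinical moulages".

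The size is given as "We aim to enrol 30 individual participants into the study who will undertake a total of 60 clinical scenarios", 30 under each condition. No allocation ratio, blocking or link between condition order and scenario order is stated. The statistical analysis paragraph names no period or scenario term. It mentions regression for unnamed confounders and within-subject comparisons.

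**The concern.** Two nuisance effects can enter a two-period comparison of this kind. Practice makes the second run differ from the first whichever scenario comes second. It cancels from the HL2 comparison when HL2 comes first as often as second. A difference in difficulty between the scenarios cancels when each scenario is run under HL2 as often as under standard care. Counterbalancing scenario order alone secures neither. The stated safeguard against learning is therefore attached to a factor that does not by itself deliver it, and the text does not tie that factor to the randomised one.

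What is at stake is precision. The hypothesis in section 10 is equivalence, which depends on a tight estimate. Section 13e says "It is not possible to perform a power calculation for this work" and gives the pilot's purpose as supplying the basis for that calculation in a later trial. Avoidable noise in the HL2 contrast works against both.

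**Working it through.** **Inputs.** 30 participants with two scenarios each (section 10): 30 × 2 = 60, which reproduces the stated total. The allocation method and the sizes of the practice effect (π) and scenario difference (δ) are not given. Two allocation cases are therefore assumed, and results are shares of π or δ.

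**1. How imbalance enters.** With treatment effect τ, a participant's HL2-minus-standard difference is τ ± π ± δ + error. The sign of π is positive when HL2 comes second. The sign of δ is positive when HL2 is used on scenario A. Averaged over 30 people:

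mean = τ + π × (HL2-second − HL2-first)/30 + δ × (HL2-on-A − HL2-on-B)/30.

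If everyone completes both runs, the difference between the two condition means equals this average, so the shares are the same for a paired or an unpaired unadjusted comparison.

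**2. Case 1: each envelope an independent 50:50 draw.** The number with HL2 first is Binomial(30, 0.5).
- Expected share of π in the estimate: 0, with SD 1/√30 = 0.183.
- P(exactly 15:15) = C(30,15)/2^30 = 0.144.
- P(18:12 or worse) = 0.362, share at least 6/30 = 0.20.
- P(20:10 or worse) = 0.099, share at least 10/30 = 0.33.

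**3. Case 2: both orders exactly 15:15 but not crossed.** The practice share is now zero. Let k be the number with HL2 first and scenario A first, which is hypergeometric (30, 15, 15). HL2 is then used on scenario A 2k times.
- Expected share of δ: 0, with SD 0.186.
- P(18:12 or worse) = 1 − P(k = 7 or 8) = 1 − 2 × C(15,7)²/C(30,15) = 1 − 2 × 6,435²/155,117,520 = 0.466.
- P(20:10 or worse): subtract P(k = 6 or 9) = 2 × 5,005²/155,117,520 = 0.323, leaving 0.143.

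**4. Effect on inference.** Simulation of 40,000 trials per setting, with no HL2 effect and a paired t-test without a period term. The practice effect is in units of the SD of the paired difference.

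| Practice effect | Order allocation | SD of estimate | Two-sided rejection rate |
|---|---|---|---|
| 0.5 | simple 50:50 | 0.205 | 5.0% |
| 0.5 | 15:15 | 0.182 | 2.8% |
| 1.0 | simple 50:50 | 0.260 | 5.3% |
| 1.0 | 15:15 | 0.182 | 0.6% |

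Mean bias was within 0.002 of zero throughout. The variance ratios are (0.205/0.182)² = 1.27 and (0.260/0.182)² = 2.04. The low rejection rates under 15:15 arise because a test without a period term still counts the practice effect as noise. Balance and a period term are both needed to realise the gain.

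**5. With four crossed sequences.** In blocks of 4, 30 = 7 × 4 + 2, so sequences hold 7 or 8 people. The largest remaining split on either balance is 16:14, a share of 2/30 = 6.7%. Period and scenario terms remove it.

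**The case against.** A reader might infer that practice and difficulty are built into the HL2 comparison, or that condition order is uncontrolled. The text does not support this. Section 10 states random assignment directly before the counterbalancing sentence, so expected bias is zero, and step 4 shows type I error close to 5% under simple randomisation.

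Nor do the documents show that the envelopes are unbalanced. Sealed envelopes conceal an allocation and say nothing about how the list was made. They may already hold a balanced list, even a four-sequence one. The sentence on scenario order could also be read loosely as covering condition order. These points stand, and they are why the figures above are conditional.

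It can also be said that list generation and model terms are often left to a randomisation procedure or an SAP. For the model terms that is fair: the absence of a period or scenario term is not itself the fault, and the planned regressions could carry both. Allocation is different. It is settled before the first participant, and a later analysis plan can adjust for imbalance but cannot create balance.

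Finally, the protocol has other safeguards: a device competency test, a resuscitation refresher, a wash-out of at least an hour, and standardised scenarios. These may shrink the practice effect and the scenario difference. The competency test is aimed at first use of the device, not at repeating a resuscitation task the same day. None of them balances HL2 against period or scenario.

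**Conclusion.** The point holds as one about unstated balance and avoidable imprecision, not about bias. As written, the protocol secures neither an even split of condition order nor an even pairing of HL2 with the two scenarios.

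Under independent 50:50 draws, there is a 36% chance that 20% or more of any practice effect stays in an unadjusted HL2 estimate. Under 15:15 on both orders without crossing, HL2 is paired 18:12 or worse with one scenario in 47% of allocations and 20:10 or worse in 14%. Each figure rests on its assumed allocation method. If the envelopes already hold a crossed, balanced list, only the statement of it is missing. The practice and scenario effects have no stated size, so the absolute distortion cannot be given. It would be negligible if both effects are small. The change is worth making because it costs almost nothing and has to be made before allocation begins.

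**What to change.** Replace the two separate statements with one concealed randomisation list of four sequences: HL2 or standard care first, crossed with scenario A or B first. Use permuted blocks, withhold the block size from recruiting staff, and put the full sequence in each sealed envelope. With blocks of 4, this gives 7 or 8 participants per sequence. State that the within-participant comparison includes period and scenario terms, which clear the remaining imbalance of up to 2/30 and take the practice effect out of the error variance.

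The cost is a new list before the first participant and a sentence or two of protocol text, with no added participants, staff or session time. The small downside is that allocations near the end of a block can become predictable in an unmasked single-site study. Varying or concealing the block size limits this. If a crossed and balanced list already exists, saying so in section 10 is enough for the allocation part.

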shared with multiple remote users via the Remote Assist application (figure 2a and b). The HoloLens™ has been used in a variety of clinical scenarios including perioperative planning, surgical training and 3D telemedicine support.(5-7)

The HL2 system therefore has significant potential for defence benefit. Specifically:

- 1) Reduction of COVID-19 transmission risk and strengthening of staff safety by reducing need for team exposure to high-risk environments (figure 2a).
- 2) Improved heads-up situational awareness and data visualisation - electronic healthcare record and imaging data can be projected into the field of view, or objects virtually marked and illustrated in the real world by remote members of the clinical team (figure 2b). Moreover, data can be captured and streamed back to wider team by the end-user in the field, who also has the ability to virtually mark targets or objects of interest.

- 3) Support the provision of remote specialist access. Specifically, Remote Assist will aid the delivery of care by permitting multidisciplinary teams to function across wide geographical areas.
- 4) Deliver remote immersive education and training - all first-person views and MR content can be captured and securely streamed for educational and training use either in real-time or on-demand.
- 5) Generation of new knowledge and capabilities - the storage of all MR content captured through the device has the potential to create a rich repository of data from which future insights and technology developments can be leveraged through human or machine learning based analysis.

[figure not shown]

Figure 3: Adaption of standard PPE for use with the HL2 system. A strip of plastic has been removed at the front of the visor.

Despite this potential, the system has yet to be formally assessed in a structured manner and therefore the benefit of MR over standard clinical practice in clinical scenarios has yet to be fully assessed, and the true value proposition has yet to be defined. It is also still unclear how the lack of physical presence of a provider impacts the teamwork, communication, and workload of a clinical team e.g. during resuscitation.

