## **10. Study Design, Method and Data Analysis**

## **Aims and objectives**

To prospectively assess the impact of HoloLens 2™ in a simulated COVID-19 setting for the assessment and resuscitation of critically unwell patients.

There are no secondary objectives for this study.

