## **Hypothesis**

Remote care delivered with the HL2 is equivalent to standard clinical practice for team performance, workload and technical performance.

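### The HL2 condition is an add-on package, so its result cannot be credited to the headset alone or read as HL2 care replacing standard practice; the hypothesis should say so

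*Protocol*

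**What the plan says.** All references are to the Protocol.

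- **Hypothesis (section 10):** "Remote care delivered with the HL2 is equivalent to standard clinical practice for team performance, workload and technical performance".
- **Aim (section 10):** "To prospectively assess the impact of HoloLens 2™ in a simulated COVID-19 setting for the assessment and resuscitation of critically unwell patients". The same paragraph says that there are no secondary objectives.
- **Background (section 9):** "It is also still unclear how the lack of physical presence of a provider impacts the teamwork, communication, and workload of a clinical team".
- **Group 1, standard care (section 10):** "A nurse, played by a member of the study team, will be provided to assist at the bedside". On access to a senior, the text says: "senior clinical support will be available by telephone if required". Patient data, algorithms and procedures are on a desktop computer. The scenario is completed by handover to a senior clinician played by the study team.
- **Group 2, HL2 supported care (section 10):** "in addition to standard care participants will complete the scenario whilst wearing an HL2 headset". A senior clinician "will be available to talk and interact directly with the participant using voice and mixed reality prompts via the HL2 throughout the simulated scenario". Patient information, algorithms and procedures can also be called up in the headset view. The description closes with: "All other standard material and equipment as per Group 1 will also be provided".
- **Use of the result:** the statistical analysis paragraph treats within-participant comparisons as showing how the technology affects the individual. Section 13e says that the pilot is meant to yield a power calculation for a later trial in patients.

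**The concern.** The hypothesis sets remote HL2 care against standard practice as if they were alternatives. The group descriptions compare standard care with standard care plus something. The something is a bundle: wearing the headset, seeing information heads-up, and having a senior within reach by voice and mixed-reality prompts for the whole scenario.

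Two misreadings could follow. If HL2 runs show fewer errors on the ICECAP tool, the gain may be credited to the headset although easier senior help produced it. If there is no difference, this may be taken to mean that the headset costs nothing, or that HL2 care can stand in for standard care. A burden from the headset may in fact have been offset by the extra support. Either reading could then travel into the later trial under the wrong label.

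Senior support could matter in this sample. The scenarios require advanced airway skills, and section 14b excludes people already independently competent in advanced airway management.

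**Working it through.** The Protocol gives no figure to reproduce here: no margin, SD, effect size, alpha or power. The check is mainly a comparison of the two conditions.

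**Step 1. What differs between conditions (section 10).**

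| Element | Standard care | HL2 supported care |
|---|---|---|
| Bedside nurse | Yes | Yes, carried over because HL2 care is additional to standard care |
| Desktop record and algorithms | Yes | Yes, carried over |
| Senior at the bedside before handover | None described | None described |
| Senior access | Telephone, if required | Voice and mixed-reality prompts via HL2, available throughout |
| Heads-up data | No | Yes |
| Headset worn | No | Yes |

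The first three rows are the same. Nobody is removed, and the senior is remote in both conditions until handover. The last three rows all change together.

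**Step 2. What can be estimated.** Let H, D and S be 0/1 indicators for headset, heads-up data and senior available throughout. With 30 participants × 2 = 60 scenarios, 30 have (H, D, S) = (0, 0, 0) and 30 have (1, 1, 1). The three columns are identical, so the data identify only

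Δ = effect of H + effect of D + effect of S (plus any interactions).

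Crossing over removes stable differences between participants, but the bundle moves with the condition. The planned regressions cannot split it either, because H, D and S never differ from one another.

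**Step 3. Illustration of masking (all inputs assumed).** Take a paired two one-sided t-test with n = 30 and one-sided alpha 0.05. The outcome has SD 1 in each condition and within-person correlation ρ. The SD of the paired difference is √(2(1 − ρ)). Equivalence with margin m is declared when the mean difference ± t × s/√30 lies inside ±m, where s is the sample SD of the differences and t the one-sided 5% critical value on 29 degrees of freedom. Suppose that the headset alone worsens errors by 0.5 SD, that m = 0.5 SD, and that the rest of the package improves errors by 0, 0.25 or 0.5 SD. Results from 40,000 simulated trials:

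| ρ | SD of difference | No offset (net 0.5) | Half offset (net 0.25) | Full offset (net 0) |
|---|---|---|---|---|
| 0.3 | √1.4 = 1.18 | 4.9% | 26.1% | 46.5% |
| 0.5 | √1.0 = 1.00 | 4.9% | 37.5% | 69.7% |
| 0.7 | √0.6 = 0.77 | 4.9% | 53.5% | 92.9% |

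With full offset, the rates match those obtained when every component is truly zero (46.5%, 69.8% and 92.8%). With m = 0.75 SD and a headset harm of 0.75 SD, the rates are about 5% without offset and 92% to 100% with full offset. The data would look the same whether the headset was harmless or harmful and compensated.

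These percentages say nothing about the likely effects in this trial. They show only that an equivalence result for the package carries no information about its parts.

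**The case against.** The strongest reply is that remote senior support is the intervention and not a nuisance. The summary (section 3) presents HL2 with Remote Assist as a telemedicine platform. Section 9 lists access to remote specialists among the intended benefits. Section 10 says that the trial evaluates mixed-reality telemedicine, and that airway skills are included to test HL2 in remote support. On that footing the natural target is HL2 supported care against usual care, and a trial need not separate the components of a package. This stands in full. It is also why the hypothesis should name the package.

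Several stronger readings are tempting, but the Protocol does not support them.

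- *The trial cannot test its hypothesis.* If remote care delivered with the HL2 means the whole Group 2 package, the two groups do compare it with standard care, and this fits the broad aim.
- *A senior is present or prompting continuously in the HL2 condition.* The text says available. It does not fix how much either the HL2 channel or the telephone is used, and it standardises the senior's role in both conditions.
- *The hypothesis claims that HL2 replaces a physically present provider.* It does not. Physical absence appears as an open question in the background and is not a stated objective.
- *Senior access must be equalised.* An open telephone line would not give the senior the shared first-person view or markings, and it would move the comparator away from on-request telephone support.
- *A headset-only effect will be carried forward.* Section 13e does not say so. If the later trial tests the same package, the package effect is the right input, provided that it is labelled as such.

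**Conclusion.** The point holds as a matter of interpretation and wording. The contrast is a legitimate one between standard care plus an HL2 package and standard care with telephone support on request. Within it, the headset is completely confounded with heads-up data and greater senior availability in all 60 scenarios, for every between-condition outcome. A result of no difference or of benefit therefore cannot be assigned to the headset alone, does not show that HL2 care can substitute for standard practice, and does not address physical absence.

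This conclusion rests on the group descriptions alone. It assumes that the bedside nurse is kept in the HL2 condition, which follows from that condition being additional to standard care. No numerical bias is claimed, because the illustration uses assumed inputs throughout. The missing equivalence margin and the choice of tests are separate matters and play no part here. The point should be fixed before the study starts, but it is not fatal to the design.

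**What to change.** Reconcile the Hypothesis with the Group 1 and Group 2 descriptions in section 10.

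1. Restate the hypothesis and the permitted conclusion along these lines: *the study estimates the effect of adding the HL2 package (headset, heads-up data and a remote senior available throughout) to standard first-responder care, compared with standard care with telephone senior support on request.* If equivalence is kept, it should be equivalence of that package comparison.
2. State that no conclusion will be drawn about the headset alone, about HL2 care substituting for standard practice, or about a provider's physical absence. Note beside the section 9 question that this design does not answer it.
3. In section 13e, label the effect carried into the later trial's power calculation as a package effect.

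The cost is Protocol wording only, with no change to participants, staff or procedures. Equalising senior access remains an optional design choice if the sponsor wants to get closer to a headset effect. It would make the comparator less like on-request telephone support, and it would leave the shared view and heads-up data as differences.
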